### 9.3. Resistance Determinations

Sequencing of the HCV NS3/4A region can be performed to monitor HCV variants present at the time points indicated in the Time and Events Schedule. Sequencing of the baseline sample will be done in real-time. Changes in sequence compared to baseline may indicate the presence of a drug resistant virus. In samples taken after baseline, the NS3/4A region may be sequenced at the

discretion of the Study Responsible Scientist based on the changes in HCV RNA levels observed in each individual subject and the limits of the sequencing assay.

Changes in the viral sequence may be evaluated by the Study Responsible Scientist but will not be regarded as AEs or SAEs.

These samples may be used by the sponsor for additional studies analyzing the genotypic and phenotypic characteristics of HCV present in these samples, upon explicit consent of the subject. No human DNA analysis will be performed on these samples.

#### **9.4. Pharmacogenomic (DNA) Evaluations**

Determination of the subject's *IL28B* genotype (single nucleotide polymorphism rs12979860) will be performed on human genomic DNA by PCR. After the results are obtained, these samples will be destroyed.

#### **9.5. Safety Evaluations**

Any clinically relevant changes occurring during the study must be recorded on the Adverse Event section of the CRF.

Any clinically significant abnormalities persisting at the end of the study/early withdrawal will be followed by the investigator until resolution or until a clinically stable endpoint is reached.

The study will include the following evaluations of safety and tolerability according to the time points provided in the Time and Events Schedule.

##### **9.5.1. Adverse Events**

Adverse events will be reported by the subject (or, when appropriate, by a caregiver, surrogate, or the subject's legally acceptable representative) for the duration of the study. Adverse events will be reported from signing of ICF until 4 weeks after last intake of study medication. Thereafter, only adverse events considered related to TMC435 will be reported. SAEs will be reported until 30 days after last study-related procedure. Adverse events will be followed by the investigator as specified in Section 12, Adverse Event Reporting.

##### **9.5.2. Clinical Laboratory Tests**

Blood samples for chemistry and hematology and a random urine sample for urinalysis will be collected. The investigator must review the laboratory report, document this review, and record any clinically relevant changes occurring during the study in the AE section of the CRF. The laboratory reports must be filed with the source documents.

For the biochemistry sample taken at screening, the subjects must have fasted overnight for at least 12 hours. For biochemistry samples taken on Day 1 and at Weeks 4, 12, and 24, the subjects must have fasted overnight for at least 10 hours. At other time points and in case the subject prematurely discontinues study medication (TMC435, PegIFN $\alpha$ -2a and RBV), please refer to the Time and Events Schedule as to whether samples need or are recommended to be taken after a

fast. In the event that values for parameters that are affected by fasting status are outside the normal range, a retest will be required after fasting.

Laboratory abnormalities will be classified by severity according to the WHO grading scale (see Attachment 2). In case a **grade 3 or grade 4** laboratory abnormality occurs, a confirmatory test should be performed by the central laboratory (or, if this is not feasible, by the local laboratory) preferably within 48 hours after the results have become available. All grade 3 and grade 4 laboratory abnormalities and laboratory abnormalities resulting in an increase of 2 grades from baseline will be followed until return to baseline or within 1 grade from baseline.

The following tests will be performed by the central laboratory:

- Hematology Panel

|                                   |                   |
|-----------------------------------|-------------------|
| -hemoglobin                       | -WBC differential |
| -hematocrit                       | Neutrophils       |
| - RBC count                       | Lymphocytes       |
| -RBC parameters:                  | Monocytes         |
| mean corpuscular hemoglobin (MCH) | Eosinophils       |
| MCH concentration (MCHC)          | Basophils         |
| mean corpuscular volume (MCV)     | -platelet count   |
| - WBC count                       |                   |

The samples will also be used for coagulation tests. Prothrombin time (PT) and activated partial thromboplastin time (aPTT) will be assessed, and the INR will be calculated.

- Chemistry Panel

|                                                                                     |                                                |
|-------------------------------------------------------------------------------------|------------------------------------------------|
| -sodium                                                                             | -uric acid                                     |
| -potassium                                                                          | -calcium (corrected for albumin)               |
| -chloride                                                                           | - phosphate                                    |
| -alkaline phosphatase                                                               | -albumin                                       |
| -lactic acid dehydrogenase (LDH)                                                    | -total protein                                 |
| -blood urea nitrogen (BUN)                                                          | - total cholesterol                            |
| -creatinine                                                                         | - high-density lipoprotein (HDL) cholesterol   |
| -glucose                                                                            | - low-density lipoprotein (LDL) cholesterol    |
| -aspartate aminotransferase (AST)                                                   | -triglycerides                                 |
| -alanine aminotransferase (ALT)                                                     | -serum magnesium                               |
| -gamma-glutamyltransferase (GGT)                                                    | -pancreatic amylase                            |
| -total, direct, indirect bilirubin                                                  | -total lipase                                  |
| -insulin a                                                               | - glycosylated hemoglobin (HbA1c) c |
| -creatinine phosphokinase (CPK)                                                     | - ANA c                             |
| -TSH (+free T 3 and free T 4 if TSH is abnormal) b |                                                |

a The homeostasis model assessment for insulin resistance (HOMA IR) index will be derived from insulin and glucose (fasted) test results at baseline, Week 4, Week 12, Week 24, Week 36, and Week 48 (as applicable).

b Safety sampling will also include a TSH test at screening, and thereafter every 12 weeks after the start of study treatment until the end of PegIFN $\alpha$ -2a and RBV treatment. In case of clinically significant abnormal TSH levels, reflex testing for free T3 and free T4 will be performed.

c The biochemistry sample taken at screening will include testing for glycosylated hemoglobin (HbA1c) and ANA.

The central laboratory will estimate the creatinine clearance (CLcr) according to the formula derived from the Modification of Diet in Renal Diseases (MDRD) study.

A midstream urine sample must be provided for local urinalysis by dipstick. If there are clinically relevant abnormalities in the investigator's opinion, further urinalysis should be done locally (e.g., sediment analysis including RBC, WBC, casts). Any clinically relevant findings from this local analysis should be reported as an AE.

- Urinalysis

- Dipstick**

- specific gravity
  - pH
  - glucose
  - protein
  - blood
  - ketones
  - bilirubin
  - urobilinogen
  - nitrite
  - leukocyte esterase

- Serum (at screening, all female subjects) and urine (at other time points, female subjects of childbearing potential only) pregnancy testing will be performed. Extra pregnancy test kits will be given if more than 4 weeks between two consecutive study visits to perform a pregnancy test at home. The results of the urine pregnancy test should be recorded in the eCRF and in the subject's medical records.
- At screening, serology for HIV-1 and HIV-2 antibody, hepatitis A immunoglobulin M (IgM), HBsAg, and anti-HCV antibody will be performed.
- At the screening visit, an additional midstream urine sample must be provided for a urine drug screen. The drug screening involves analysis for amphetamines, benzodiazepines, cocaine, cannabinoids, barbiturates and opioids.
- At screening a schistosomiasis antibody test will be performed. If the schistosomiasis antibody test is positive, a schistosomiasis antigen blood test or rectal snip should be performed.
- At the screening visit, AFP will be tested for all subjects. FSH will be tested for female subjects who are postmenopausal for less than 2 years.
- In case of rash, safety blood samples must be taken, at unscheduled visits, as described in Section 9.5.7.1, and are to be processed by the local laboratory. The following parameters need to be tested: AST, ALT, sedimentation rate and a complete blood cell count (including hemoglobin, hematocrit, RBC count, WBC count, neutrophils, lymphocytes, monocytes, eosinophils, basophils, platelet count) and creatinine.

### **9.5.3. Electrocardiogram (ECG)**

ECG will be performed locally for screening purposes only. If clinically indicated, additional ECG measurements can be performed at the discretion of the investigator.

During the collection of ECGs, subjects should be in a quiet setting without distractions (e.g., television, cell phones). Subjects should rest in a supine position for at least 5 minutes before ECG collection and should refrain from talking or moving arms or legs. If blood sampling or vital sign measurement is scheduled for the same time point as ECG recording, the procedures should be performed in the following order: ECG(s), vital signs, blood draw.

### **9.5.4. Vital Signs**

Systolic and diastolic blood pressure (SBP, DBP) and pulse rate will be recorded according to the Time and Events Schedule.

Blood pressure and pulse/heart rate measurements will be assessed supine with a completely automated device. Manual techniques will be used only if an automated device is not available.

Blood pressure and pulse/heart rate measurements should be preceded by at least 5 minutes of rest in a quiet setting without distractions (e.g., television, cell phones).

### **9.5.5. Physical Examination**

To evaluate the subject's eligibility, a physical examination will be performed at screening. In addition, a physical examination will be performed at several time points throughout the study.

A physical examination includes review of the following systems: general appearance, gastrointestinal system, skin and mucous membranes, eyes, ears, nose, throat, cardiovascular system, respiratory system and genito-urinary system. A neurological and musculo-skeletal examination will be performed as well as a check of the lymph nodes. Other findings will be reported in case the physical examination reveals a clinically significant abnormality not present in this list.

Physical examination at screening should include a fundoscopic eye examination, as per the manufacturer's prescribing information for PegIFN $\alpha$ -2a. Note: Baseline fundoscopic pathology which would require routine follow up on PegIFN $\alpha$ -2a and RBV therapy is considered exclusionary, as per exclusion criterion 7.

To obtain the actual body weight, subjects must be weighed lightly clothed. The height should be measured barefoot at the screening visit.

Any clinically relevant changes occurring during the study must be recorded on the Adverse Event section of the eCRF.

### **9.5.6. Patient-reported Symptoms, Functioning, and Quality of Life**

Five PRO instruments included in this study will be used to prospectively assess symptoms, functional impairments, and HRQoL that subjects experience during and after HCV treatment.

The HCV-SIQ, FSS, CES-D, WPAI:Hepatitis C, and the EQ5D will be completed by subjects at time points indicated in the Time and Events Schedule. Study personnel will instruct subjects in how to self-administer the PRO instruments. If subjects require assistance reading the PRO questionnaires, trained study personnel may read the questions and responses aloud to the subject and record the subject's response on the questionnaire form. Subjects should not be advised by anyone (study personnel, family or others) regarding which answer to give on the PRO questionnaires. For more detailed information about administration of the PRO, please refer to the study manual.

For further guidance, see also Section 9.1.3.

#### **9.5.6.1. Hepatitis C Symptom & Impact Questionnaire**

The HCV-SIQ (Attachment 3) is a self-administered questionnaire containing 30 items developed to assess severity or frequency of 26 symptoms associated with HCV or its treatment and 4 questions regarding the impact of symptoms on work/school attendance and daily activities.

Based on information from screening and baseline assessments, a scoring system will be developed for comparison of symptoms and their impact over the course of treatment and follow-up. Three scores will be evaluated as secondary endpoints in this study: a symptom severity score consisting of the sum of responses to the 26 symptom items, a missed work/school score, and a daily activity impairment score. Higher scores indicate worse symptom severity, more time missed from work/school, and more impairment in daily activities, respectively. Measurement properties of the HCV-SIQ have not been evaluated; psychometric evaluation of the HCV-SIQ scores including possible alternative scoring to improve utility of HCV-SIQ scores will be explored as part of this study.

HCV-SIQ symptom scores based on body systems may better characterize symptom experiences during treatment and follow-up. Preliminary scoring by body system will be developed based on data from the screening and baseline visit.

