| 1. Sore or achy muscles or joints                                                                                                                                                                                                                              |  0 |  1 |  2 |  3 |  4 |
| 2. Feverish (for example feeling hot, cold, sweating)                                                                                                                                                                                                          |  0 |  1 |  2 |  3 |  4 |
| 3. Headache                                                                                                                                                                                                                                                    |  0 |  1 |  2 |  3 |  4 |
| 4. Queasy or nauseous                                                                                                                                                                                                                                          |  0 |  1 |  2 |  3 |  4 |
| 5. Stomach pain or cramps                                                                                                                                                                                                                                      |  0 |  1 |  2 |  3 |  4 |

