| 21. Dry mouth                                                                                                                                                                                                                                                  |  0 |  1 |  2 |  3 |  4 |
| 22. Ringing or buzzing sound in ears                                                                                                                                                                                                                           |  0 |  1 |  2 |  3 |  4 |

| How many of the past 7 days have you had the following symptoms? | 0 days                                | 1-2 days                              | 3-4 days                              | 5-6 days                              | Every day                             |
|------------------------------------------------------------------|---------------------------------------|---------------------------------------|---------------------------------------|---------------------------------------|---------------------------------------|
| 23. Diarrhea (very loose or liquid stools)                       |  0 |  1 |  2 |  3 |  4 |
| 24. Loss of appetite/did not feel like eating                    |  0 |  1 |  2 |  3 |  4 |

| Over the past 7 days, did you notice that ...                           | Yes                                   | No                                    |
|-------------------------------------------------------------------------|---------------------------------------|---------------------------------------|
| 25. Things tasted bad or had little flavor                              |  0 |  1 |

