| 26. Your hair or nails felt dry, looked dull, or tended to break easily |  0 |  1 |

| PART 2: Impact on Daily Life                                                                                        |                                                                                                                    |                                                                                                                             |                                                                                                                      |
|---------------------------------------------------------------------------------------------------------------------|--------------------------------------------------------------------------------------------------------------------|-----------------------------------------------------------------------------------------------------------------------------|----------------------------------------------------------------------------------------------------------------------|
| 27. Over the past 7 days, how much did your health limit you doing things you needed to do? (mark one answer only)  |                                                                                                                    |                                                                                                                             |                                                                                                                      |
| Not at all limited

I did everything
I needed to do
 0 | A little limited

I did most things
I needed to do
 1 | Somewhat limited

I could not do many things
I needed to do
 2 | Very limited

I could not do anything
I needed to do
 3 |

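### Summing the printed HCV-SIQ codes makes symptom items 25 and 26 run against the stated direction of the symptom score, and the protocol states no recode

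*Protocol*

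**What the plan says.** Section 9.5.6.1 describes the HCV-SIQ as "30 items developed to assess severity or frequency of 26 symptoms associated with HCV or its treatment and 4 questions" on impact. It names three scores as secondary endpoints. The first is "a symptom severity score consisting of the sum of responses to the 26 symptom items", and for it "Higher scores indicate worse symptom severity".

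Attachment 3 prints a number beside every response box:

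- Items 1 to 22 (from "1. Sore or achy muscles or joints" onwards) run from 0, not at all, to 4, extremely.
- Items 23 (diarrhea) and 24 (appetite) run from 0, no days, to 4, every day.
- Under the stem "Over the past 7 days, did you notice that", the last two symptom items, "25. Things tasted bad or had little flavor" and "26. Your hair or nails felt dry, looked dull, or tended to break easily", have a Yes box printed 0 and a No box printed 1.

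Section 9.2.2 lists mean change from baseline in the HCV-SIQ symptom score, at each visit, under Other Secondary Endpoints.

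Scoring is partly left open. Section 9.5.6.1 also says that a scoring system will be developed from screening and baseline data. Section 11.4 has the SAP propose HCV-SIQ scoring, and Section 11.5 plans an interim analysis of screening and baseline PRO data for that purpose.

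**The concern.** The plan fixes three things about this score: which items enter, that they are added, and which way the total points. The printed codes of two of the 26 items are incompatible with the third. For items 1 to 24 a larger number means a worse symptom; for items 25 and 26 the larger number means that the symptom is absent. No reversal is written for the HCV-SIQ, although Attachment 7 prints one for the positively worded CES-D items.

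If the printed codes were summed as they stand, taste or hair and nail symptoms that emerge on treatment would count as improvement, and their resolution as worsening. Two reversed items would also tend to lower item-total correlations and internal consistency. That matters here because Section 3.2 gives evaluation of the instrument's validity and reliability as a purpose of collecting these data, and Section 9.5.6.1 says that its measurement properties have not yet been evaluated.

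**Working it through.** **Inputs.** Item counts and codes are from Attachment 3; the sum and its direction are from Section 9.5.6.1.

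**Item count.** 22 severity items + 2 frequency items + 2 yes/no items = 26 symptom items; with 4 impact questions, 30. This agrees with Section 9.5.6.1.

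**Score from the printed codes.** Let T be the total of items 1 to 24 (0 to 24 × 4 = 96) and y the number of Yes answers to items 25 and 26 (0, 1 or 2).

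- Printed codes: S = T + (2 − y)
- Recoded Yes=1, No=0: S* = T + y

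| Subject | T | y | Printed codes | Recoded |
|---|---|---|---|---|
| No symptoms | 0 | 0 | 2 | 0 |
| Items 1–24 at worst, 25 and 26 absent | 96 | 0 | 98 | 96 |
| All 26 at worst | 96 | 2 | 96 | 98 |

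Both versions span 0 to 98. With the printed codes, however, the maximum is reached only when two of the symptoms are absent, and a symptom-free subject does not have the lowest score.

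**Change in one subject.** Suppose T is unchanged and both symptoms appear, so y goes from 0 to 2.

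- Printed codes: change = −2
- Recoded: change = +2
- Error = −2 − (+2) = −4 points, the largest possible for one subject

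**Mean change.** Suppose the prevalence of each symptom rises by d between baseline and a visit. The mean of y then rises by 2d.

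- Printed codes contribute −2d; recoded codes contribute +2d
- Error = −2d − 2d = −4d points

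| d (assumed) | Printed | Recoded | Error |
|---|---|---|---|
| 0.1 | −0.2 | +0.2 | −0.4 |
| 0.3 | −0.6 | +0.6 | −1.2 |
| 0.5 | −1.0 | +1.0 | −2.0 |
| 1.0 (ceiling) | −2.0 | +2.0 | −4.0 |

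Here d is the net rise in prevalence from baseline, not the share of subjects who ever report the symptom. The protocol gives no figure for it. If prevalence falls, d is negative and the error changes sign. The two items account for 2 of the 98 points.

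**The case against.** The strongest reply is that the protocol has not finished defining this score. Section 9.5.6.1 announces scoring development next to the definition, Section 11.4 passes the proposed scoring to the SAP, and Section 11.5 sets up an interim analysis to establish and test it. Coding direction is an ordinary detail of a scoring algorithm, and the SAP, which is not at hand, may already contain the recode. Testing on screening and baseline data could also expose two items that run against the other 24, though this is not certain if few subjects have these symptoms before treatment.

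Second, the protocol never says that the printed numbers are score values. Item 28, a filter question on school or paid work, carries the same Yes=0/No=1 codes, which suggests a data-entry convention across the form. The stated direction would then oblige a programmer to align the two items.

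A reader might therefore infer more than the documents support, namely that the trial will report a reversed score. Only the literal reading is established: the printed codes, summed, contradict the stated direction.

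What does not stand is that nothing needs correcting. The deferrals leave development and alternative scoring open, but they do not withdraw the items, the addition or the direction that Section 9.5.6.1 already states. The printed numbers are the only values that the protocol supplies for adding up. Section 17.4 has the forms completed on paper and then keyed by a CRO, so these may well be the values that reach the database. If they are entry codes, a recode is needed and should be written, as it is for the CES-D.

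**Conclusion.** The contradiction is real and minor. As written, the sum of the printed codes for 26 items cannot be a score in which higher always means worse, because two items point the other way. The error is at most 4 points in one subject's change score and −4d points in the mean change, on a 98-point range. Any particular mean bias rests on an assumed net rise in prevalence, and all of these figures assume that the printed codes are summed without a recode.

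The endpoint is an other secondary, descriptive PRO measure in an uncontrolled study, with no hypothesis test attached. SVR12 and the sample size do not depend on it, and Section 9.1.3 says that questionnaire answers are not used to determine adverse event reporting. The error can be undone at analysis from the item responses. A reader might infer that the PRO results as a whole are unreliable; two items worth 2 of 98 points in one of several scores do not support that.

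**What to change.** Add one sentence to Section 9.5.6.1 or beneath the form in Attachment 3, and carry it into the SAP: items 25 and 26 are recoded Yes=1, No=0 before the 26 symptom items are summed. Apply it before the screening/baseline scoring analysis of Section 11.5, so that the score is developed and tested on correctly directed items, and to any body-system or alternative score that contains either item. The score then runs from 0 (no symptoms) to 98 (all symptoms at their worst), as the stated direction requires.

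The cost is one line of text and one line in the scoring program. The printed form and the data already collected need not change. If the SAP already contains this recode, a cross-reference from Section 9.5.6.1 is enough.
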